## Abstract

**Background:**

Dengue virus (DENV) infection poses a major global public health burden, particularly in endemic regions where repeated exposure increases the risk of severe disease. Despite revisions to the World Health Organization (WHO) dengue classification, early prediction of progression to severe dengue remains challenging due to overlapping clinical and laboratory features. Current management strategies rely primarily on supportive care and reactive monitoring, underscoring the need for predictive biomarkers that enable early risk stratification and timely intervention.

**Discussion:**

This study aims to generate comprehensive systems-level insights into host–virus interactions driving dengue severity and to identify biomarkers predictive of disease progression. The findings may inform improved patient triage, early intervention strategies, and the identification of novel therapeutic targets.

**Trial registration:**

ClinicalTrials.gov ID NCT06751836 Registration Date: December 13, 2024, CTRI/2022/10/046293 (MAHE) Registration Date: October 10, 2022.

## Background

Dengue is a mosquito-borne viral infection with a wide clinical spectrum ranging from self-limiting febrile illness to life-threatening severe dengue characterized by plasma leakage, hemorrhage, and organ failure [1]. Transmitted primarily by *Aedes aegypti* and *Aedes albopictus* mosquitoes, the virus encompasses four antigenically distinct serotypes (DENV-1 through DENV-4), each capable of inducing both primary infection and, upon subsequent exposure to a heterologous serotype, a more severe immunopathological response [2]. Globally, dengue continues to expand geographically, placing nearly half of the world’s population at risk. The World Health Organization (WHO) estimates approximately 390 million dengue infections annually, of which roughly 96 million manifests clinically (WHO fact sheet, Dengue August 2025, https://www.who.int/news-room/fact-sheets/detail/dengue-and-severe-dengue). Over the past two decades, reported case counts have increased eight-fold, driven by urbanization, increased international travel, climate change, and inadequate vector control measures. Dengue is now endemic in more than 100 countries across tropical and subtropical regions of the Americas, South-East Asia, the Western Pacific, Africa, and the Eastern Mediterranean.

Early identification of patients at risk of severe disease remains one of the most pressing challenges in dengue clinical management [3, 4]. The clinical course of dengue is characteristically triphasic, encompassing a febrile phase (days 1–3), a critical phase (days 4–6) during which plasma leakage may precipitate dengue shock syndrome, and a recovery phase. The overlap of clinical features across severity strata particularly during the early febrile phase renders timely risk stratification both critical and elusive.

Despite the 2009 WHO dengue classification system, which introduced “warning signs” as clinical predictors of severe dengue, evidence regarding their individual and combined predictive value remains inconsistent [3, 5]. Laboratory markers such as leukopenia, thrombocytopenia, and elevated hematocrit are routinely monitored; however, their sensitivity and specificity for predicting progression to severe dengue are suboptimal when assessed in isolation. Biomarkers including NS1 antigen levels, inflammatory cytokines, and endothelial permeability indices have shown promise in exploratory studies but have yet to be validated prospectively in diverse clinical settings [3, 6].

No validated, widely applicable clinical prediction tool currently exists that integrates bedside clinical features, routine laboratory parameters, and emerging biomarkers to accurately stratify patients by severity risk, despite progress in understanding dengue pathophysiology. This gap results in significant heterogeneity in clinical decision-making ranging from unnecessary hospitalizations that strain healthcare resources to premature discharge of high-risk patients [7]. The consequences are particularly severe in resource-limited endemic settings, where intensive care capacity is constrained and case fatality rates can exceed those in well-resourced environments [8]. 

Recent advances in high-throughput multi-omics technologies have fundamentally transformed the capacity to interrogate host responses to infectious diseases. The ability to simultaneously characterize transcriptomic, proteomic, and metabolomic alterations from a single biological sample offers an unprecedented systems-level perspective on host–pathogen interactions, enabling the identification of molecular signatures that transcend single-platform observations and more faithfully capture the biological complexity underlying disease severity [9]. 

The COMBAT study aims to address this gap by employing a multidisciplinary, systems biology approach to identify molecular signatures and pathways associated with dengue severity across geographically distinct endemic regions. The identification of predictive biomarkers and mechanistic pathways may support earlier dengue risk stratification, improve clinical management, and inform the development of novel therapeutic strategies.

## Methods/design

### Study aim

The COMBAT clinical study aims to identify and validate host molecular biomarkers and dysregulated biological pathways associated with dengue disease severity using an integrated multi-omics systems biology approach in dengue-endemic populations.

#### Primary objectives

To determine dengue virus serotypes and characterize host cytokine profiles across dengue severity categories.To identify transcriptomic, proteomic, metabolomic, and glycomic signatures associated with dengue disease severity.

#### Secondary objectives

To integrate transcriptomic, proteomic, metabolomic, and glycomic data to identify dysregulated immune and metabolic pathways associated with disease progression.To validate candidate biomarkers and pathways in geographically independent cohorts.To investigate mechanistic host pathways influencing dengue severity using in vitro models informed by clinical multi-omics findings.

### Study design

COMBAT is a prospective, multicenter, observational longitudinal study designed to characterize host responses to dengue infection without altering standard clinical management.

### Study setting

The study is conducted at clinical sites in two dengue-endemic regions, Guatemala (Central America) and India (Southeast Asia). Guatemala is an exemplary location for studying the DENV infection, owing to its distinctive combination of climatic diversity and endemic and dengue presence. Samples are collected from different hospitals following report of the outbreak. Under the India-EU cooperation on research & innovation (R&I) and co-funding partnership under the EU framework program on R&I “Horizon Europe”, samples are also collected from three hospitals in India, i.e., the Artemis Hospital and Max Health Care (a unit of Devki Devi Foundation) in New Delhi and Kasturba Hospital, Manipal, Karnataka (with diagnostic facility at Manipal Institute of Virology, MAHE, Manipal, Karnataka). Those are the two epicentres of the dengue endemic in India.

### Study cohorts

Blood samples from patients are collected as per the WHO revised 2009 case classification [1] as: (1) dengue without warning signs (DwoWS), (2) dengue with warning signs (DWS) and (3) severe dengue (SD). Additionally, non-dengue samples will be collected from DENV-negative healthy controls (HCs). 100 individuals from each category will be collected in Guatemala and will serve as the discovery cohort, while 150 individuals from each category will be collected from India and serve as the validation cohort. The patient inclusion and exclusion criteria are presented in Table 1. Additional cohorts from Guatemala, Brazil and Honduras will be used for further validation of the dengue severity biomarkers. Validation of any additional cohorts requires a local ethical clearance, as well as approval from both the Swedish Ethical Review Authority and the COMBAT General Assembly.

**Table 1 Tab1:** Inclusion and Exclusion Criteria for patient enrolment

Inclusion Criteria: The criteria for enrolling the patients in the respective groups.
**Group 1**: Dengue without warning signs (DwoWS) Patients presenting with the following symptoms and confirmed positive for dengue infection following anti-dengue IgM or NS1 ELISA (Enzyme-linked Immunosorbent Assay) lab tests. Symptoms are fever along with at least two of the following: • Myalgia, arthralgia • Nausea and/or vomiting • Rashes • Leukopenia
**Group 2**: DENV with warning signs (DWS) Patients with the above symptoms and any of the following clinical signs: • Abdominal pain with tenderness • Persistent vomiting • Fluid accumulation • Mucosal bleeding • Restlessness, lethargy • Liver enlargement >2 cm • Laboratory findings: An increase in hematocrit levels and a rapid decrease in platelet count
**Group 3**: Severe dengue (SD) Patients with: • Severe plasma leakage leading to hypovolemic shock (dengue shock syndrome) and fluid accumulation with respiratory distress • Severe bleeding, such as epistaxis, and internal bleeding, evaluated by a clinician • Severe organ involvement with any of the following symptoms: - Liver AST or ALT ≥ 1000 - CNS: impaired consciousness - Heart and other organs failure
**Exclusion criteria**: Individuals with the following characteristics were not enrolled.
• Patients below the age of 18 years • Pregnant, immunocompromised or undergoing chemotherapy, on steroids or immunosuppressive drugs in the last year or with liver cirrhosis • Co-infection with a non-dengue pathogen • Cases with a lab-confirmed dengue infection within the past three months

The study is designed to investigate the progression of dengue infection in patients, from without warning signs, to with warning signs to severe dengue, which varies between cases. If a patient recruited in the category “DwoWS” develops symptoms correlating with severity and receives intensive care, they will then be re-categorized into the second “DWS” or third “SD” group. Keeping in mind the complexity of dengue presentation, subcategorization of the patients will be performed as necessary to establish the degree of severity depending on the timepoint of recruitment and the points of sample collection. The highest (peak) severity category reached during the acute illness constitutes the participant’s definitive severity classification and serves as the primary outcome label for all biomarker analyses. For incorporation into the biomarker discovery and validation analyses, the earliest sample for each participant collected before or at the point of clinical deterioration is used as the predictor, and the definitive peak severity category is used as the outcome.

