#### Artificial intelligence (AI) models for DENV severity

The assessment of DENV severity using traditional methods has proven difficult due to many contributing factors, such as variation in symptoms, dynamic nature of dengue infection, and lack of specific biomarkers, amongst others [8]. Multiple machine-learning and deep-learning models, including logistic regression, random forests, XGBoost, support vector machines, multilayer perceptrons, and multimodal neural-network architectures, will be trained and systematically compared for DENV severity prediction. The models will integrate available clinical, laboratory, demographic, virological, and multi-omics data, using feature-selection and dimensionality-reduction approaches. Model interpretability will be assessed using explainable AI approaches, including SHapley Additive exPlanations (SHAP) and Local Interpretable Model-agnostic Explanations (LIME), to identify the variables and molecular features driving individual- and cohort-level predictions. Temporal and geographical robustness will be evaluated using time-split validation, external validation across sites, and leave-one-site-out cross-validation. Model performance will be assessed using AUROC, AUPRC, sensitivity, specificity, F1-score, calibration, and decision-curve analysis to identify clinically robust and generalizable models for DENV severity prediction.

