### Study status

Prospective recruitment and sampling commenced in January 2025 and is ongoing at all participating sites. As of June 2026, 170 participants had been enrolled across the four study groups (DwoWS, DWS, SD and healthy controls) in the Guatemala (discovery) cohort; recruitment of the India (validation) cohort is initiated in July 2026 following the funding body approval. Recruitment is anticipated to be completed by November 2027, or earlier should the target sample size (100 participants per group in the discovery cohort and 150 per group in the validation cohort) be reached sooner. Because dengue transmission is cyclical and epidemic-dependent, recruitment timelines are contingent on local outbreak dynamics; should enrolment at any site fall behind target, pre-specified additional cohorts and biobanked samples will be accessed as a mitigation strategy, subject to approval by the COMBAT General Assembly.

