#### Secondary endpoints

Dysregulated immune and metabolic pathways associated with disease severity, identified through integrative multi-omic analysis.Reproducibility of candidate biomarkers and pathways in the independent India (validation) cohort and additional external cohorts.Discrimination and calibration performance of machine-learning models integrating clinical, laboratory, demographic, virological and multi-omics features for severity prediction.Analytical and clinical performance of the focused 5–10 biomarker Olink^®^ Flex dengue severity panel.Associations between DENV serotype, host immunometabolic profile and disease severity.

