Despite these limitations, the study has notable strengths. Its prospective, multicenter design across geographically distinct endemic regions with harmonized sample collection and protocols enables evaluation of host responses under diverse epidemiological conditions. The inclusion of both discovery and validation cohorts enhances the robustness and generalizability of findings. Moreover, the multi-omics systems biology framework provides a comprehensive platform for characterizing immune and metabolic pathways associated with disease progression. Mechanism-based biomarker discovery offers a major advantage over traditional biomarker discovery in viral diseases because it identifies markers that are directly linked to the biological processes driving disease progression [24]. Rather than relying only on statistical associations between individual markers and clinical outcomes, mechanism-based approaches integrate transcriptomic, proteomic, metabolomic, immunological, and clinical data to define the pathways underlying viral replication, immune activation, endothelial injury, metabolic dysregulation, and organ damage. This improves biological interpretability and increases the likelihood that biomarkers are reproducible across cohorts, disease stages, and populations [17].

The operational challenges encountered during implementation reflect broader weaknesses in dengue surveillance and outbreak preparedness. Dependence on clinical diagnosis, under-detection of mild cases within hospital-based systems and shifting transmission patterns contribute to uncertainty in disease burden estimates and complicate early identification of patients at risk of deterioration. By identifying host biomarkers and dysregulated pathways linked to severe outcomes, the COMBAT study seeks to advance earlier risk stratification and more informed triage decisions. Such predictive tools could support more efficient allocation of healthcare resources during outbreaks and help reduce dengue-related morbidity and mortality. Beyond its immediate relevance to dengue, the integrated clinical, laboratory, and systems biology framework developed in COMBAT offers a model for strengthening preparedness against other emerging viral infections with heterogeneous clinical manifestations. In doing so, the study advances not only dengue research but also epidemic resilience and translational public health research capacity in endemic regions.

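### Equal targets per severity group fix the severe-dengue share near one third in both cohorts, so unweighted calibration, decision curves, AUPRC and F1 describe the quota mix and not a clinical population

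*Protocol article*

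**What the plan says.** Under Study cohorts, the protocol article plans that "100 individuals from each category will be collected in Guatemala and will serve as the discovery cohort, while 150 individuals from each category" will be recruited in India as the validation cohort. The categories are dengue without warning signs (DwoWS), dengue with warning signs (DWS), severe dengue (SD) and healthy controls. Study status treats the same numbers as the point at which recruitment may end early, "should the target sample size (100 participants per group in the discovery cohort and 150 per group in the validation cohort) be reached sooner". It also reports that by June 2026, in Guatemala, "170 participants had been enrolled across the four study groups (DwoWS, DWS, SD and healthy controls"), with India starting in July 2026.

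The outcome for all biomarker analyses is peak severity: "The highest (peak) severity category reached during the acute illness constitutes" the definitive classification.

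The section on AI models states: "Model performance will be assessed using AUROC, AUPRC, sensitivity, specificity, F1-score, calibration, and decision-curve analysis", and gives the purpose as "to identify clinically robust and generalizable models for DENV severity prediction". Calibration is also a secondary endpoint: "Discrimination and calibration performance of machine-learning models integrating clinical, laboratory, demographic, virological and multi-omics features for severity prediction". The Discussion says the study seeks to "advance earlier risk stratification and more informed triage decisions".

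The article names no target severe-dengue rate. The limitations mention that cohort composition may vary, but not that the outcome rate is set by the recruitment targets.

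**The concern.** Participants are recruited by severity category, which is the outcome to be predicted or close to it. That suits differential expression, where equal groups give good power. It does not suit measures that depend on how common the outcome is. Calibration, net benefit, AUPRC and F1 all take their value partly from the share of severe cases, and here the investigators choose that share.

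A second effect works through the non-severe group. DwoWS and DWS are forced to 1:1, and SD is presumably harder to separate from DWS than from DwoWS. Specificity and the pooled AUROC therefore depend on this mix, although they do not depend on the severe rate as such.

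India has the same targets as Guatemala. A model can look well calibrated and useful in both cohorts, yet overstate risk in a setting where severe dengue is less common. These are the measures by which clinically robust models are to be identified, and one of them is a named endpoint.

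**Working it through.** **Where the target comes from.** The Statistical analysis section gives 20,000 genes, 100 prognostic, fold change 2, mean count 5, dispersion 0.5, power 0.8 and FDR 0.01.

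- Per-gene significance level: 100 × 0.8 × 0.01 / (19,900 × 0.99) = 4.06 × 10⁻⁵.
- A two-sided exact negative-binomial test has power 0.793 with 66 per group and 0.804 with 67, so the stated 67 reproduces.
- With 30% loss, 67 / 0.7 = 95.7, that is 96, which fits the target of 100.

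The sample size is not in error. It comes from a two-group expression comparison and not from the case mix of presenting patients.

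**Severe share implied by the targets.**

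- Among dengue patients: 100/300 = 150/450 = 33.3%, or odds of 0.5.
- With healthy controls included: 100/400 = 150/600 = 25%.
- DWS among the non-severe: 100/200 = 150/300 = 50%.

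**Effect of moving to another rate.** The documents give no natural rate *p*, so 2% to 20% is assumed. The illustrative rule has sensitivity (Se) and specificity (Sp) of 0.80, also assumed. For AUPRC, a binormal score with that operating point is used (AUROC 0.88).

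- Factor by which predicted odds are too high: 0.5 / [p/(1−p)].
- True risk behind a prediction of 50% (odds 1): true odds = [p/(1−p)] / 0.5.
- Precision = Se·p / [Se·p + (1−Sp)(1−p)]; F1 = 2 × precision × Se / (precision + Se).
- Net benefit at threshold t = 0.20: Se·p − (1−Sp)(1−p) × t/(1−t), where t/(1−t) = 0.25.

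| Severe rate | Odds too high by | Predicted 50% is truly | F1 | AUPRC | Net benefit at 20% |
|---|---|---|---|---|---|
| 33.3% (targets) | 1 | 50% | 0.73 | 0.80 | +0.233 |
| 20% | 2.0 | 33% | 0.62 | 0.70 | +0.120 |
| 10% | 4.5 | 18% | 0.44 | 0.55 | +0.035 |
| 5% | 9.5 | 9.5% | 0.29 | 0.41 | −0.008 |
| 2% | 24.5 | 3.9% | 0.14 | 0.25 | −0.033 |

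For example, at 5%: 0.80 × 0.05 − 0.20 × 0.95 × 0.25 = 0.0400 − 0.0475 = −0.0075. The rule breaks even where 0.80p = 0.05(1−p), that is p = 0.05/0.85 = 5.9%. At the quota rate it beats treating everyone: 1/3 − (2/3) × 0.25 = +0.167, against +0.233.

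**Mix within the non-severe.** With w the share of DwoWS among the non-severe, pooled specificity is w × Sp(DwoWS) + (1−w) × Sp(DWS). The targets set w = 0.5. The documents give no natural value of w, so no size is put on this effect.

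**The case against.** The strongest reply is that the article is silent on weighting and does not rule it out. It lists the metrics in one sentence, and correction to a target rate is the kind of detail an analysis plan carries. That stands as far as method goes: the absence of a weighting formula is no defect in a condensed article. But the article does fix the sampling scheme, the metrics and the use to be made of them. Weights also need counts of eligible patients by category, and a later analysis plan cannot create counts that sites did not keep.

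Other objections limit the point:

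- A reader might infer that predicted risks will be too high in every real clinic. The documents do not support that. They give no natural rate, recruitment is hospital-based during outbreaks, and at 10% and 20% the illustrative net benefit stays positive.
- A reader might infer that the study cannot inform triage. AUROC and sensitivity do not depend on the severe rate, the triage wording is an aim, and reweighting or recalibration would address the problem.
- Positive predictive value is not a planned metric. Precision enters above only as a step towards F1.
- The net-benefit column holds sensitivity and specificity fixed. A planned decision curve would classify by predicted risk, so the column shows dependence on the rate and does not forecast the trial's curve.
- Exactly 33% is a target. Re-categorisation to peak severity, uneven sample loss and the fallback to additional or biobanked samples could shift it.
- It would be too strong to say that validation must miss the problem. The targets apply per cohort and not per site, so leave-one-site-out and time-split checks may meet other mixes, as may the additional cohorts from Guatemala, Brazil and Honduras, whose case mix is not described. The main India validation shares the same targets and is unlikely to reveal it.

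**Conclusion.** The concern holds in this form: the equal targets set the severe share near one third in both cohorts, so unweighted calibration, net benefit, AUPRC and F1 describe the quota mix. Specificity and pooled AUROC carry the forced 1:1 mix of DwoWS and DWS.

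The size depends on a rate that the documents do not give. Over an assumed 2% to 20%, predicted odds would be 24.5 to 2 times too high. The illustrative rule changes from benefit to harm at about 5.9%. The odds figures assume that marker distributions within severe and non-severe patients carry over to the target population. The F1 and net-benefit figures also rest on the assumed sensitivity and specificity of 0.80. The distortion from the severe rate vanishes only if that rate among the intended patients is near one third.

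This should be fixed, but it does not undermine the study. The sample size reproduces, differential expression is unaffected, and neither primary endpoint names an affected metric. What is at stake is a secondary endpoint and the basis for calling a model clinically robust.

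**What to change.** 1. Define the target population for the prediction models and its expected severity mix.
2. From now on, log at each site the number of confirmed, eligible adult dengue patients by category. For Guatemala participants already enrolled, reconstruct these counts from hospital records where possible; where not, use a stated range.
3. Compute calibration, decision curves, AUPRC and F1 with category-specific inverse-sampling weights. An intercept offset alone is not equivalent. In a logistic model it corrects the rate of SD against non-SD, but not the DwoWS:DWS mix. The other models need weighting or recalibration of their predicted risks.
4. Report these metrics over a range of severe-dengue rates.
5. Report AUROC and specificity separately for SD against DWS and SD against DwoWS.
6. Keep healthy controls out of all severity-prediction metrics.

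If this is not feasible, limit the calibration and clinical-utility claims to the quota sample and say so among the limitations in the Discussion.

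The recruitment targets need not change. The cost is record-keeping at the sites, retrospective work across several hospitals for the 170 Guatemala participants enrolled by June 2026, and weighted estimates that are less precise and probably less favourable. India was due to start in July 2026, so counts can be kept there from or near the start if the change is made promptly.

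### Table 1 draws the line between dengue with warning signs and severe dengue inconsistently, and that line is the primary outcome label

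*Protocol article*

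**What the plan says.** The section Study cohorts states that "Blood samples from patients are collected as per the WHO revised 2009 case classification", and Table 1 sets out the groups.

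- **Group 2 (DWS):** "Patients with the above symptoms and any of the following clinical signs". The list includes "Fluid accumulation • Mucosal bleeding", so either sign alone is enough once the Group 1 symptoms are present. Neither carries a grade.
- **Group 3 (SD), plasma leakage:** "Severe plasma leakage leading to hypovolemic shock (dengue shock syndrome) and fluid accumulation with respiratory distress".
- **Group 3, bleeding:** "Severe bleeding, such as epistaxis, and internal bleeding, evaluated by a clinician".
- **Group 3, organs:** "Severe organ involvement with any of the following symptoms". This is the only SD bullet with an explicit any-of. The Group 3 list as a whole opens without saying whether one bullet or all are needed.

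The text after Table 1 makes "The highest (peak) severity category reached during the acute illness" the participant's definitive classification and the outcome label for every biomarker analysis. The second primary endpoint (Study endpoint) is a validated panel that predicts progression to severe dengue.

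**The concern.** The DWS/SD boundary is the outcome variable of the prediction endpoint. If two careful readers of Table 1 can give the same patient different labels, the outcome is not fixed by the document that defines it.

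Guatemala is the discovery cohort and India the validation cohort. If their sites read the table differently, a panel that fails to replicate could not be told apart from one whose target was labelled differently. Mislabelling within a cohort also mixes the two groups and shrinks the molecular differences between them.

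**Working it through.** The point rests on wording, so the main check sets the criteria side by side.

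**Step 1. Bleeding.** The DWS entry covers any mucosal bleed. The SD entry requires severe bleeding and gives epistaxis as its example. A nosebleed is bleeding from a mucosal surface, so it falls under the DWS entry and is also the illustration of the SD entry. Table 1 sets no threshold between them.

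**Step 2. The operators.** *And* joins two items in both the plasma-leakage bullet and the bleeding bullet. Take three patients with the Group 1 symptoms and no other SD feature, and apply each consistent reading of *and*, assuming that any one bullet suffices:

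| Patient | *And* as joint requirement | *And* as list of alternatives |
|---|---|---|
| Nosebleed judged severe, no internal bleeding | DWS (mucosal bleeding) | SD |
| Shock and fluid accumulation, no respiratory distress | DWS (fluid accumulation) | SD |
| Fluid accumulation with respiratory distress, no shock | DWS (fluid accumulation) | SD |

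All three labels change with the reading. The upward risk (a nosebleed counted as SD) belongs to the second reading and the downward risk (shock or distress left in DWS) to the first. One consistent reading does not produce both, but nothing in the table fixes the reading, and a site could read adjacent bullets differently.

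**Step 3. Does the wording elsewhere settle it?** Table 1 marks alternatives explicitly in other places: and/or for nausea and vomiting, *or* for AST and ALT, any-of for Group 2 and for the organ bullet. That favours the joint reading. Against it, requiring both epistaxis and internal bleeding is implausible. The Background says that plasma leakage may precipitate dengue shock syndrome, and the Discussion lists plasma leakage, hemorrhage and shock as severe outcomes. Neither asks for respiratory distress as well. The article points both ways.

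**Step 4. Can the label be rebuilt later?** Table 2 lists AST and ALT but no bleeding, shock or respiratory-distress item. From the listed items, labels resting on bleeding or plasma leakage could not be re-derived without the charts.

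**Step 5. Illustration of size, under assumed error rates.** First, the plan's own figure. The inputs from Statistical analysis are 20,000 genes, 100 prognostic, FDR 0.01, power 0.8, control count 5, dispersion 0.5 and fold change 2.

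- Per-test alpha = 80 × 0.01 / (19,900 × 0.99) = 4.06e-5, two-sided.
- Variance term = (1/5 + 0.5) + (1/10 + 0.5) = 1.3.
- n = (z for alpha/2 + z for power)² × 1.3 / (ln 2)² = 66.2, so 67 per group, as stated.

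Now let a share e of labelled SD truly be DWS and a share h of labelled DWS truly be SD. A true fold change of 2 is observed as [2(1−e) + e] / [(1−h) + 2h] = (2−e)/(1+h). The group means become 5(1+h) and 5(2−e). The squared z-sum is 66.18 × (ln 2)² / 1.3 = 24.46.

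| e | h | Observed fold change | Variance term | n per group |
|---|---|---|---|---|
| 0.10 | 0.05 | 1.90/1.05 = 1.81 | 1/5.25 + 1/9.5 + 1 = 1.296 | about 90 |
| 0.20 | 0.10 | 1.80/1.10 = 1.64 | 1/5.5 + 1/9 + 1 = 1.293 | about 130 |
| 0.30 | 0.10 | 1.70/1.10 = 1.55 | 1/5.5 + 1/8.5 + 1 = 1.299 | about 168 |

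The values of e and h are not in the article. Any non-zero error takes a true fold change of exactly 2 below 2, so that result is built in. The calculation ignores the extra within-group spread that mixing adds, and the article does not say that SD versus DWS is the contrast it sized.

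**The case against.** The other side has several fair points.

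- **Qualifiers on bleeding.** Table 1 does not name epistaxis under DWS, and the SD entry demands severe bleeding evaluated by a clinician. A reader might infer that any nosebleed becomes SD. The text does not support that. What stands is that severity has no threshold and the one named example belongs to both tiers.
- **Ordered scale.** Meeting both a lower and a higher tier is normal, and the peak rule assigns the higher. This answers double assignment. It does not say when the higher tier has been met.
- **Loose connector.** *And* may simply list manifestations, and the organ-failure bullet may bring some patients with shock or respiratory distress into SD. Both are possible, but neither is stated.
- **External standard.** A reader might infer that the boundary is wrong against WHO 2009. The article cites that classification without reproducing its wording, so only internal inconsistency can be shown here.
- **Site differences.** A reader might infer that the two countries will label differently. The article reports harmonized protocols and data curation, so this is a risk and not a prediction.
- **Condensed article.** Grading rules and operators may sit in the full protocol or case report form. That would excuse silence. Here the table states criteria, and as stated they conflict.

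**Conclusion.** The DWS/SD boundary in Table 1 is internally inconsistent and can err in either direction, depending on how *and* and the epistaxis example are read. Because this boundary supplies the outcome label for all biomarker analyses, it should be corrected even though the defect is one of wording.

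The number of participants affected is unknown. The fold changes of 1.81, 1.64 and 1.55 show only what the assumed error rates would do. They do not show that the study is underpowered. The conclusion assumes that sites apply Table 1 as printed, without a fuller definition elsewhere.

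**What to change.** - Reconcile the Group 2 and Group 3 bleeding entries so that the same event does not illustrate both tiers.
- State the and/or operators within each Group 3 bullet, and state whether one bullet is enough or more are needed.
- Align both groups with the WHO 2009 classification that the study says it follows. Which clinical thresholds apply is for the investigators to settle from that source.
- Issue the same wording to the Guatemala and India sites. Study status gives July 2026 for the start of recruitment in India, so early correction limits the re-checking there.
- Re-check the labels of Guatemala dengue participants whose category rests on bleeding or plasma leakage. The 170 enrolled by June 2026 include healthy controls, who need no re-check.

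The cost is a wording change and a limited chart review. Some participants may move between groups, which would alter the count towards the target of 100 per group.
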